###### Main and secondary outcomes

Given that the broad MoveEarly intervention is targeted at promoting whole-child development, designating one primary outcome a priori is challenging. As a single test is not capable of capturing multiple aspects of a child’s development, we will determine effects across multiple relevant outcomes. Whilst regarding children’s movement competence and creativity as priority outcomes, we are cautious about defining the River Challenge as the main outcome given its unknown measurement properties and lack of data to allow a sample size calculation. If the River Challenge demonstrates acceptable measurement properties, we will designate movement competence and creativity as the main outcomes, and other aspects of children's development as secondary outcomes.

###### Secondary aims

####### **Secondary analyses of intervention effects**

Evidence shows that PA interventions in school may be most beneficial for those most in need [170, 171] and more beneficial for boys than for girls [172]. Thus, we will include analyses of effect moderation by sex, age, socioeconomic status, and baseline levels of outcomes. We will also test for mediation effects to explore possible mechanisms, given significant intervention effects. Mediation analyses may include half-longitudinal (2 timepoints) or full (3 timepoints; given available data for relevant mediators) mediation models using SEM [164].

####### **Association analyses**

Cross-sectional and longitudinal association analyses will be used to study correlates and determinants of child behaviours and development. Longitudinal analyses will include both groups (intervention and control) to increase power, if there are trivial intervention effects. Growth models will be used to determine reciprocal relationships among variables over time [164]. In addition to standard regression models, we will use multivariate pattern analysis to explore multivariate association patterns among the included variables [133, 173]. Multivariate pattern analyses will be performed using the package *mvpaShiny* v. 0.0.0.9000R [173] in R v. 4.3.2, [174]/RStudio v. 2023.09.1 [175], while other analyses will apply the same statistical models and softwares as specified above.

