### Objectives and research questions

Connecting and developing ideas and concepts across disciplinary boundaries is a prerequisite to developing quality solutions to complex societal challenges. In response to the need for an integrated perspective on the role of movement, play, and exploration in young children, we will design and test an integrated early years pedagogy to provide a synthesis of contemporary perspectives across disciplines and to stimulate new transdisciplinary theoretical, methodological, experimental, and empirical research in the ECE field. We propose MoveEarly as an efficient, acceptable, and feasible solution to child development challenges and to shift societies toward a more active, flourishing, and sustainable way of life. In response to low staff qualifications, we will raise competence and facilitate implementation of the move-play-explore pedagogy by offering ECE staff a quality professional development program structured within a continuing education model. An online resource will be an essential part of this program, supporting implementation of MoveEarly and later scaling. To understand kindergarten contexts and staff needs and to allow all parties to buy in, the intervention will be co-created between researchers, users, and stakeholders. This is crucial for designing both a good intervention and an informed process evaluation.

In response to the need for broader evaluation of interventions in young children, we will develop and use new outcomes of movement competence, creativity and well-being. We will use qualitative approaches to obtain a deeper understanding of children’s perceptions and particularly how exploration and interaction with their physical and social environment facilitate and consolidate learning. Beyond outcome evaluation, we will conduct a thorough process evaluation to explain discrepancies between expected and observed outcomes (on an individual and organizational level) to better understand how context influences outcomes. By identifying the mechanisms of implementation, we will inform scaling of the intervention in the real world.

The main objectives of MoveEarly are to develop and test:a novel ECE pedagogical approach integrating movement, play, and exploration as conceptual cornerstones for improved child developmenta novel professional development and resources for the ECE workforce to implement movement, play, and exploration in their everyday practice

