### Process evaluation

Given that MoveEarly is framed within a “realist RCT” approach [73], a complex systems perspective will be used to explore the deeper (sociological) mechanisms by which the kindergartens interact with the intervention [68]. The initial program theory, described in Sect. " Intervention and theoretical framework", states that by enhancing staff competence and motivation to integrate the move-play-explore pedagogy into kindergarten’s daily operations, we expect to find positive effects on children’s health, development, well-being, and learning. This causal pathway, and how it varies according to individual and contextual factors, will be examined in the process evaluation, which seeks to provide a general overview as well as a deeper insight into how staff and children in the intervention kindergartens respond to the MoveEarly professional development and integrate the move-play-explore pedagogy into staffs’ and children’s daily practices. Thus, the process evaluation will explore what works for whom, under what circumstances, and why, within the MoveEarly intervention. As suggested by McGill et al. [194], we will use a 2-phase framework for the process evaluation that seek to assess change over time from a complex systems perspective. The first phase will involve producing a description of the system and identifying hypotheses about how the system change in response to the MoveEarly intervention. The second phase will involve adapting the planned evaluation approach in accordance with the pathways of the emergent findings.

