##### Quantitative data

In sample 1, we will analyse between-group effects on an individual and institutional level. In sample 3, we will analyse between-group effects or main effects of time among intervention kindergartens on an institutional level. Analyses will follow the approaches and procedures outlined in Sect. "Development of measures of movement competence, creativity, playfulness, explorative behaviour and well-being in young children" but will additionally apply Generalized Estimating Equations to model categorical data from questionnaires [223]. Analyses of potential moderators or mediators will be performed as described inSect. "Secondary aims", using both process and outcome evaluation data on the child and kindergarten level.

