Beyond undertaking professional development and implementing the proposed pedagogical principles, a sufficient contrast in practices between intervention and control kindergartens is required to find any effects on a child level. Given that the concepts of movement, play and exploration are covered in the curricula for kindergartens in Norway [96], all core elements of the pedagogy is present in both intervention and control kindergartens. Since we are not providing a standardized “programme” for kindergartens to implement but “pedagogical principles” to guide their practice along with the tools and support, the contrast between groups is hard to predict. Evidence suggest both approaches (i.e., prescribed programs or guiding principles) may be equally effective [26]. Another prerequisite to reveal effects is the ability of outcome measures to capture potential intervention effects. While it is a strength of the study that we include a tailormade measure of movement competence and creativity and a range of commonly applied measures of health and development applicable for young children, we have a broad intervention and generic measures of child health and development. This approach contrasts, for example, proof-of-concept studies showing favourable effects of physically active learning on closely related learning outcomes [227, 228]. However, we aim to design an enriched pedagogical approach that ECE practitioners find meaningful and applicable and that easily can be adopted by kindergartens as a universal early years pedagogy. While it may be challenging to deliver the intervention both on a kindergarten (i.e., staff professional development) and child level (i.e., pedagogical practice), we argue that testing such an approach is critical to develop quality practices and inform policy development. Adding to the outcome evaluation, we include a thorough process evaluation to capture to which extent the intervention is implemented and institutionalized in kindergartens and how, under which conditions and for whom it may work [73]. This is critical to aid interpretation of our findings and improve knowledge of implementing complex interventions in the ECE sector and beyond.

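### Mediation is tested only after a significant intervention effect, so the indirect-effect estimate is withheld for the outcomes whose missing effect most needs explaining

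*Protocol article*

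**What the plan says.** Under Secondary aims, in the part on secondary analyses of intervention effects, the article says: "We will also test for mediation effects to explore possible mechanisms, given significant intervention effects". Moderation, in the same paragraph, carries no such condition.

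The process evaluation's section on quantitative data takes the rule over: "Analyses of potential moderators or mediators will be performed as described" under Secondary aims, using both process and outcome data at child and kindergarten level.

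Three other places bear on it:

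- Objectives and research questions: "we will conduct a thorough process evaluation to explain discrepancies between expected and observed outcomes".
- Process evaluation, on the chain from staff competence and motivation through daily practice to the child: "This causal pathway, and how it varies according to individual and contextual factors, will be examined in the process evaluation". No significance condition appears here.
- Outcome evaluation, Analysis plan, Primary aim: significance is p ≤ 0.05, but effect patterns across variables carry most weight in the conclusions.

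**The concern.** A child outcome that was expected to improve and shows no significant effect is a discrepancy between expected and observed results. The rule switches off the one planned analysis that formally joins the two links of the programme theory in exactly that case. It also lets a p-value decide whether mechanism is examined, in a plan that otherwise puts p-values below patterns.

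A significant total effect is not a logical precondition for mediation. An indirect effect can be present and estimable when the total effect is not significant. The protocol expects uncertainty here: its background says effectiveness trials in this setting have generally not succeeded, and its Discussion notes that "a sufficient contrast in practices between intervention and control kindergartens is required to find any effects on a child level" and that this contrast is hard to predict. At stake is how much the trial can say about why an outcome did not move, which its authors want for scaling.

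**Working it through.** **1. What depends on significance and what does not**

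| Question | Planned analysis | Depends on significance? |
|---|---|---|
| Did staff practice or staff activity change? | "In sample 1, we will analyse between-group effects on an individual and institutional level" (25-item practice questionnaire, staff accelerometry, all kindergartens) | No |
| Did children change? | Intention-to-treat comparison | No |
| Does practice go with child outcome? | Association models; "Longitudinal analyses will include both groups (intervention and control) to increase power, if there are trivial intervention effects" | No |
| How much of the effect runs through practice? | Mediation by structural equation modelling | Yes |

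Only the last row is lost for a non-significant outcome. The text does not say whether the condition works outcome by outcome or for the trial as a whole.

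**2. The protocol's own figure**

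Inputs from the sample-size section: m = 9 children per cluster, CV = 0.65, ICC = 0.05 to 0.10.

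DE = 1 + ((CV² + 1) × m − 1) × ICC, where (0.4225 + 1) × 9 − 1 = 11.80.

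- ICC 0.05: 1 + 11.80 × 0.05 = 1.59 (stated 1.60)
- ICC 0.10: 1 + 11.80 × 0.10 = 2.18 (stated 2.19)

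The stated design effects reproduce to within 1%.

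**3. How often would a true effect be significant?**

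With n = 25 × 9 = 225 per arm and baseline adjustment (variance factor 1 − r²), power = Φ(d / √(2/n_eff) − 1.96), where n_eff = 225 / (DE × (1 − r²)). A two-sided test is assumed.

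- Better case, DE 1.60 and r 0.7: n_eff = 225 / (1.60 × 0.51) = 275.7
- Worse case, DE 2.19 and r 0.6: n_eff = 225 / (2.19 × 0.64) = 160.5

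| True d | Better | Worse |
|---|---|---|
| 0.11 (low end cited for cognition) | 25% | 17% |
| 0.16 (low end cited for academic achievement) | 47% | 30% |
| 0.25 (low end of detectable range) | 84% | 61% |
| 0.27 (cited for physical activity) | 89% | 68% |
| 0.40 (high end of detectable range) | 99.7% | 95% |

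The complement is the chance that a real effect of that size gets no mediation analysis.

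**4. Could an indirect effect be detected when the total effect is not significant?**

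This is an illustration only. A simulation at kindergarten level (25 v 25, 2000 runs per setting) assumed full mediation through one kindergarten-level mediator that allocation shifts by 0.8 to 1.5 SD, measured without error and unconfounded with the outcome. None of this is in the protocol. The indirect effect counted as detected when both links were significant.

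| True d | Indirect effect detected | Detected, but total effect not significant |
|---|---|---|
| 0.11 | 26–73% | 22–53% |
| 0.16 | 47–92% | 34–54% |
| 0.25 | 77–99% | 12–38% |

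At d = 0.25, the 0.8 SD shift in the better case is excluded because it would need more outcome variance than is available. A noisy self-rated mediator, or partial mediation, would be expected to lower the detection figures.

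**The case against.** The strongest reply is that little is lost. The practice questionnaire and staff activity are compared between randomised arms in all kindergartens, and researcher-rated practice is observed in 8 intervention and 4 control kindergartens. Child outcomes are analysed by intention to treat. A null on practice, or a change in practice with no change in children, can be read from those comparisons without a mediation model. The practice-to-child link is not randomised inside a mediation model either. The task of explaining discrepancies is given to a realist, mixed-methods evaluation that also tests context-mechanism-outcome configurations; mediation is a secondary, exploratory tool.

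Most of this stands. A reader might infer that the trial could not separate implementation failure from theory failure, or that in a mixed trial the whole quantitative test of the programme theory disappears. The documents do not support either. The comparisons just listed are unconditional, and on the natural reading mediation would still run for the outcomes that are significant.

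A reader might also stress chance selection: with 15 to 20 independent null outcomes, at least one would reach p ≤ 0.05 in 1 − 0.95¹⁵ = 54% to 1 − 0.95²⁰ = 64% of trials. Neither the count nor independence comes from the protocol, and this is a general multiplicity matter, not a cost specific to this rule.

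What the reply does not answer is that the association models are not committed to staff-practice data and do not yield an indirect effect, and that the process evaluation's own mediator analyses inherit the condition. Because the rule is stated in the protocol, it is not a detail left open for a later analysis plan.

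**Conclusion.** The point holds in a limited form. For any child outcome without a significant intervention effect, the protocol withholds the joint estimate of allocation to practice to child outcome. That fits poorly with its aim of explaining discrepancies and with its own ranking of patterns above p-values. For true effects at the low end of those it cites (0.11 to 0.16), this would happen in roughly 53 to 83% of trials, and at 0.25 in 16 to 39%. These figures assume 225 children per arm, baseline-adjusted analysis, the stated design effects and correlations, a two-sided 5% test, and the condition applied outcome by outcome. How often a detectable indirect effect would be missed rests on assumed mediator strength and is illustrative only. The primary inference is not affected. It is a cheap improvement.

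**What to change.** Delete the clause that makes mediation depend on significant intervention effects. For the main outcomes, state that each link (allocation to mediator, mediator to outcome) and the indirect effect will be reported with confidence intervals whatever the p-value of the intervention effect, and labelled exploratory. The cross-reference in the process evaluation then needs no further change.

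Choose mediators measured before the outcome. Practice self-assessment is planned at baseline, 12 and 24 months, and children are measured at baseline, 7 and 18 months, so for 18-month child outcomes the usable follow-up practice score is the 12-month one. Staff activity at 7 months also qualifies, as does child activity during care hours at 7 months if it is among the outcomes selected for that visit.

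The cost is a change of wording and modest analysis time, with no new data collection. The downside is that some imprecise indirect estimates will be reported.

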#### Development of measures of movement competence, creativity, playfulness, explorative behaviour and well-being in young children

##### Background

To focus on young children’s holistic development rather than school readiness, new measurement tools are required which evaluate relevant aspects of children’s movement, play and exploration. We will develop measures that capture young children’s skillfulness, adaptability and creativity in and through movement, along with their playfulness, explorative behaviour and well-being. The new or adapted instruments will focus on how children adapt and explore movement solutions in a range of contexts or scenarios and how kindergarten staff consider their behaviours in care, therefore making these tools, not only valid and reliable, but also feasible and relevant.

Whilst there are several validated instruments that assess fundamental movement skills [176], their scale of analysis is the organism with a focus on only one optimal movement pattern in a closed decontextualized environment. Thus, the nature and structure of these measures remove the embodied and embedded nature of play [49, 75]. New measures are needed that assess how young children can adapt and extend movement solutions in a range of movement, play, and exploration contexts. To be specific and relevant to kindergarten-aged children, this requires measures that are more representative of play. We have developed a measurement instrument based on the theoretical concepts of ecological dynamics, where environmental and task constraints encourage the emergence of adaptive behaviours [177], and also on the theory of Compound Flexibility [178], which links adaptability in a child’s play environment with opportunities to explore and the effect these can have on children’s well-being. The instrument therefore includes aspects of movement adaptability encouraged by changes to the environment and creativity encouraged by substantial flexibility in the child’s responses.

There is limited research into the measurement of play and exploration. This could be because the concepts of play and exploration are difficult to define and measure [179]. However, the outcomes of such behaviours could be measured. For example, during play, aspects such as playfulness, enjoyment and engagement [180, 181] could be observed. Capturing a child’s well-being can be challenging as there are broad and differing definitions of this concept, with many including multiple domains of well-being [182]. We developed an instrument to capture children’s well-being within the context of movement, play and exploration in kindergartens. This would be most suitably captured within a child’s natural environment, rather than in a standardized laboratory situation. Thus, we developed a staff-report observation instrument which aims to capture kindergarten staff’s perceptions of children’s playfulness, exploratory behaviour and well-being.

##### Design and methods

A systematic literature review was undertaken to learn what has already been done with regard to the measurement of movement, play and exploration. This was registered with PROSPERO (reference number CRD 42023396648). The analysis and reporting will be based upon the Preferred Reporting Items for Systematic Reviews and Meta-Analyses (PRISMA) statement [183]. We searched for publications which investigate the validity and/or reliability of any measurement instruments assessing play, exploration and/or creativity and instruments assessing movement including play, exploration and/or creativity.

The laboratory assessment instrument (River Challenge) was guided by and extends tools such as the Movement Ability Test [184] and the Thinking Creatively in Action and Movement test [185]. We planned that the new instrument should have the following features:

The design of several carefully constructed playful challenges will be inspired by observations of children’s free play, ensuring these are relevant to the age group involved. The challenges will be based on stories to help engage children in the challenges and to encourage playfulness.Through these challenges, each of which has key information and constraints for children to perceive and regulate action, the play environment will invite children to functionally apply and adapt various locomotor, object control, and balance skills.Scoring of movement competence will be based on functionality (success or not, irrespective of how the challenges are solved), which is a key concept of ecological dynamics. Scoring of creativity will be based on fluency and originality.

The staff-report observation instrument (Children’s Involvement and Well-being in Movement, Play and Exploration Questionnaire) was designed to capture facets of children’s playfulness, exploration, and well-being in everyday play settings. Existing measurement scales exist, such as The Children’s Playfulness Scale [180], which aim to capture playfulness, and the Leuven Involvement and Wellbeing Scale [186], which aims to capture well-being. However, as the intention of the research is to capture exploration, playfulness and well-being, a revised staff report observation instrument is justified. The staff-report observation instrument was designed as a multi-item questionnaire for staff to reflect on the children’s involvement, experiences and reactions within the kindergarten environment over the past month, where each child’s behaviours are scored on a 5-point Likert scale.

The development of both instruments builds on our research team’s extensive experience with test batteries that have been used in large studies and historical and cultural analyses of children’s play and exploration activities. The two instruments was developed using the process for instrument development suggested by de Vet et al. [187]. Each instrument was piloted, revised and adapted before field testing. We will determine measurement properties as recommended by the Consensus-based standards for the selection of health measurement instruments group [188], using in-person and video scoring of children.

